#### Secondary Clinical Aims

We will also examine clinical data, including the diary data and the HIT-6 score. The 24-hour daily diary, successfully used in a previous UNC study, collects hourly headache experience for 18 weeks [34]. To examine the role of headache frequency, we will use the diary data to construct summary measures of headache experience for each day, including the number of headache hours in a day and the number of hours with moderate-severe headaches. With the repeated measurements of headache hours per day as the outcome variable, we will construct random-effects Poisson regression models with treatment as the exposure, and age and sex as covariates, to examine the association between the diets, blood fatty acids and their derivatives, and headache.

To test the effects on quality-of-life, we will construct a regression equation with the final HIT-6 score as the outcome variable, the treatment group as the exposure variable and the baseline HIT score as the control variable. We will also test a limited number of interaction effects to see whether the treatment effects vary by sub-groups (e.g., gender, age). In addition, controlling for the baseline score, we will examine the relationship between the post-intervention HIT score and post-intervention %n-6 in HUFA.

#### Handling of Missing Data

Every effort will be made to contact participants who fail to complete required study instruments. Based on our experience with UNC headache patients, we anticipate that only a small proportion will not complete the study. Through missing information evaluation, we will assess whether drop-outs depend on any patient characteristics. If necessary we will do multiple imputations in the analysis.

#### Power calculations

Assuming that the %n-6 in HUFA will be on average 0.8, 0.5 and 0.3 at the end of the 12 weeks (as predicted by Lands empirical equation [31] and the nutrient intake targets) and a common standard deviation set at the maximum value of 0.5, we determined that, to achieve 80% power, we need 32 individuals per each arm. Repeated measures power-analysis procedures indicate that we will have adequate power (close to 80%) to test the time interaction effect with 32 persons measured over 4 time points (Aim 2).

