### Randomization

At the first treatment visit, study participants are randomized to 1 of 2 diets, a low n-6 diet, or a low n-6 plus high n-3 diet (Figure 1 and Table 1), to be maintained for 12 consecutive weeks. Randomization employs a computer algorithm using a random number sequence to generate a permuted block of 4-8 subjects, ensuring equal numbers of participants in each arm of the study [33]. The program, accessed only through an on-line interface by the study dietitian, also documents treatment assignment in an un-editable form with a date stamp.

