Adherence with the daily diary has been excellent, with 83.3% of participants completing at least 80% of daily entries. Most have tolerated the diets well; they have demonstrated diet adherence via changes in erythrocyte fatty acids. Preliminary analysis of composite erythrocyte fatty acid data of the first 20 participants, with blinding preserved (i.e., both diet groups are analyzed together and investigators remain masked to diet group), reveals significant reductions in %n-6 in HUFA and n-6 AA and LA, and significant increases in n-3 EPA, DHA and the omega-3 index compared with baseline erythrocyte fatty acids over the 12-week intervention (Table 5).

**Table 5 T5:** Means of erythrocyte fatty acids over the 12-week intervention, Chronic Daily Headache study, May 2010

	Baseline (n = 20)		Week 4 (n = 20)		Week 8 (n = 20)		Week 12 (n = 18)	
	
Variable	Mean	95% CI	Mean	95% CI	Mean	95% CI	Mean	95% CI
Omega-3 index	4.4	3.9, 5.0	6.2	5.4, 7.1	7.0	5.9, 8.1	7.8	6.5, 9.0
% n-6 in HUFA*	76.3	74.5, 78.0	70.4	67.5, 73.2	67.4	63.7, 71.0	64.7	60.3, 69.0
DHA	4.0	3.5, 4.5	5.2	4.5, 5.8	5.7	4.9, 6.5	6.3	5.4, 7.3
EPA	0.46	0.39, 0.54	1.1	0.8, 1.3	1.3	0.95, 1.6	1.4	1.0, 1.8
AA	14.8	14.5, 15.2	14.4	13.7, 15.1	13.8	13.2, 14.5	13.7	12.9, 14.5
LA	11.5	10.8, 12.1	9.5	8.8, 10.2	9.3	8.6, 10.0	9.5	8.8, 10.3

* %n-6 in HUFA is the percentage of omega-6 fatty acid in total HUFA as calculated by: 100 × (20:3n-6 + 20:4n-6 + 22:4n-6 + 22:5n-6)/(20:5n-3 + 22:5n-3 + 22:6n-3 + 20:3n-6 + 20:4n-6 + 22:4n-6 + 22:5n-6 + 20:3n-9).

Abbreviations: HUFA, highly-unsaturated fatty acid; DHA, Docosahexaenoic acid; EPA, eicosapentaenoic acid; AA, arachidonic acid; LA, linoleic acid.

Based on our current rates of recruitment, we expect to have a sufficient number of participants to complete the study 2 1/2 years after the first patient was enrolled. Based on these numbers, we should have adequate power to test our hypothesis of differential %n-6 HUFA in both plasma and erythrocyte lipid pools. Examination of the clinical data of the study (HIT-6, daily diaries) should allow us to predict effect sizes for a larger clinical trial.

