### Limitations

The primary methodological limitation for interpreting the primary outcome (%n-6 in HUFA) and other metabolic outcomes of this trial is the limited duration of 12 weeks. Industrialized populations consuming large quantities of LA-rich seed oils maintain large quantities of n-6 LA in adipose tissue. In the US, adipose tissue LA increased from about 6% of total fatty acids in 1960 [52,53] to about 18% in 1986 [54], which coincided with an increase in dietary LA from about 2 en% in 1909 to 7 en% in 1999 [55]. Because n-6 and n-3 fatty acids have a half-life of about 1 to 2 years in adipose tissue [56-58], the 12-week dietary period employed in this trial may not be of sufficient duration for plasma and erythrocyte PUFAs to reach dynamic equilibrium. Our preliminary blinded analysis of erythrocyte fatty acid data is consistent with the expectation that maximal reductions in plasma and tissue LA and/or AA may not occur over 12 weeks; AA and %n-6 in HUFA continued to decline, and EPA, DHA, and the omega-3 index continued to increase between 8 and 12 weeks (Table 5).

The primary methodological limitation for interpreting the clinical outcomes of this trial is the lack of a control group consuming average US amounts of individual n-6 and n-3 fatty acids. This will limit the ability to determine if changes in clinical outcomes (headache frequency, intensity, and quality-of-life) are due to the diets themselves, to the expectation of benefits associated with participation in a clinical trial, or to the placebo effect of the interventions. This study was not designed to test the clinical efficacy of the dietary interventions. However, the study does demonstrate that, with support, free-living subjects can successfully modify their diets enough to result in significant changes in erythrocyte fatty acids, setting the stage for a larger, fully powered randomized controlled trial of clinical efficacy in CDH or another chronic pain population.

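### The stated 32 per arm at 80% power does not follow from the stated inputs: three means are given for a two-arm trial, and no pair of them with SD 0.5 yields 32

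*Protocol article*

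**What the plan says.** The sample size rests on one sentence under Power calculations. It takes three end-of-intervention means for the primary outcome, as proportions: "Assuming that the %n-6 in HUFA will be on average 0.8, 0.5 and 0.3 at the end of the 12 weeks". It attributes them to an empirical equation and the intake targets, uses "a common standard deviation set at the maximum value of 0.5", and concludes that "to achieve 80% power, we need 32 individuals per each arm". No mean is assigned to an arm, and neither alpha nor sidedness is given there.

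Elsewhere the design has two groups. Under Randomization, "study participants are randomized to 1 of 2 diets", in permuted blocks "ensuring equal numbers of participants in each arm of the study". Under Analysis of Aim 1, the first step is a t-test between the two groups on transformed proportions at 12 weeks, followed by a regression that adjusts for baseline and other covariates. Under Eligibility, 76 are to be randomized, with at least 80% expected to complete.

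The Results then report blinded, pooled erythrocyte data (Table 5) and say of the primary hypothesis that "we should have adequate power to test our hypothesis of differential %n-6 HUFA in both plasma and erythrocyte lipid pools".

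**The concern.** A two-arm comparison needs two means, a common SD, alpha and power. Here there are three means, so at least one does not describe an arm and the reader cannot tell which difference the trial was sized to detect. Each pair implies a very different sample size, so the ambiguity matters.

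The SD is also doubtful. A value of 0.5 is the ceiling for a 0/1 variable with mean 0.5. The outcome is a percentage measured in each participant, and Table 5 already shows how much it varies.

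At stake is how the result will be read. If the between-diet difference is not significant, readers will judge it against an 80% power figure that the inputs do not produce. The difference the trial can in fact detect is not stated.

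**Working it through.** **Inputs.** Means 0.8, 0.5 and 0.3; SD 0.5; power 80%; 32 per arm (Power calculations). Two arms, 1:1 (Randomization). Two-group t-test (Analysis of Aim 1). Assumption: alpha 0.05, tried two-sided and one-sided.

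**Step 1: try to reproduce 32 per arm.** The normal approximation is n = 2(z₁₋α⸝₂ + z₀.₈)² × SD² / difference². For 0.8 vs 0.5, two-sided, this is 2 × (1.960 + 0.842)² × 0.25 / 0.09 = 43.6. The exact t-test (noncentral t) gives slightly more:

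| Contrast | Difference / SD | n per arm, two-sided | n per arm, one-sided | Two-sided power at 32 per arm |
|---|---|---|---|---|
| 0.8 vs 0.5 | 0.6 | 44.6 (45) | 35.0 | 66% |
| 0.5 vs 0.3 | 0.4 | 99.1 (100) | 78.0 | 35% |
| 0.8 vs 0.3 | 1.0 | 16.7 (17) | 13.1 | 98% |

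Using all three means in a one-way ANOVA, the standard deviation of the means is 0.2055, so f = 0.2055 / 0.5 = 0.411. That needs about 20 per group for 80% power; 32 per group would give 95%.

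Working backwards, 32 per arm at SD 0.5 gives 80% power for a standardized difference of 0.711, that is 0.711 × 0.5 = 0.356 two-sided, or about 0.31 one-sided. The available differences are 0.2, 0.3 and 0.5. None matches.

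**Step 2: can 0.5 be a common SD?** A variable confined to 0–1 with mean m has SD at most √(m(1 − m)):

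- m = 0.8: √0.16 = 0.40
- m = 0.5: √0.25 = 0.50
- m = 0.3: √0.21 = 0.46

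So 0.5 is unattainable at two of the three assumed means. At the third it requires every participant to be at 0 or 1.

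**Step 3: SD implied by Table 5.** At week 12, n = 18, mean 64.7, 95% CI 60.3 to 69.0. SD = half-width × √n / t₀.₉₇₅,₁₇ = 4.35 × 4.243 / 2.110 = 8.7 points, or 0.087. The chi-square interval for the SD is 6.6 to 13.1 points (0.066 to 0.131). This pools both diets, so it includes any difference between them.

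**Step 4: assumed means against Table 5.** Two arms with means of 50% and 30% pool to at most 50% whatever the split, and to 40% if equal. The observed interval starts at 60.3%.

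**Step 5: detectable difference on the blinded data** (two-sided 5%, 80% power, untransformed scale):

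- 32 analysed per arm: 0.711 × 8.75 = 6.2 points. Over the SD's interval: 0.711 × 6.56 = 4.7 to 0.711 × 13.11 = 9.3 points.
- The protocol's minimum retention gives 76 × 0.80 = 60.8 completers, about 30 per arm. The standardized difference is then 0.736, and 0.736 × 8.75 = 6.4 points.

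**The case against.** The strongest reply is that 0.5 was chosen openly as a ceiling. If the true SD is far smaller, the calculation is conservative and the trial is safe. This largely stands as regards the trial's actual power: at SD 8.7 points, 32 per arm has over 99% power for a 10-point difference, and at SD 13.1 points still 85%. It does not rescue the sentence, because the ceiling, put through the planned test with the stated means, still does not give 32.

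Other routes to 32 can be found, but the text states none of them. One-sided two-proportion formulas for 0.8 vs 0.5 give 30 to 31, but they discard the stated SD and treat a continuous outcome as binary. A baseline-adjusted analysis with correlation 0.53 brings 44.6 down to 44.6 × (1 − 0.53²) = 32, but no correlation is given. A three-group ANOVA reaches 32 per group at 95% power, but the stated power is 80% and there is no third arm.

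Table 5 also has limits. It is preliminary, pooled, untransformed, from 18 participants at week 12, and covers erythrocytes only, whereas the primary outcome also covers plasma. It counts against arm means of 50% and 30% in erythrocytes and says nothing about plasma.

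A reader might take 0.5 and 0.3 as the two diets, with 0.8 as usual diet, and conclude that the trial has 35% power and needs 100 per arm. The document does not support that. It assigns no mean to an arm, and the 35% depends on an SD about six times the one Table 5 implies.

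**Conclusion.** The point holds as an error in the stated calculation. Three means are given for two arms, and 32 per arm at 80% power follows from no pair of them at SD 0.5, two-sided or one-sided, under the planned unadjusted t-test, nor from a three-group ANOVA. The two-sided requirement ranges from 17 to 100 per arm depending on the pair. This rests on alpha of 5%, which is assumed.

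The SD of 0.5 is not a possible common value at these means, and the blinded week-12 estimate is about one sixth of it.

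It would go too far to infer that the trial is underpowered. The SD and the assumed differences are both large, and they act on power in opposite directions. The defect is that the 80% figure, and the Results statement that relies on it, have no demonstrated basis, and that the difference the trial can detect is not reported.

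**What to change.** - State which two-arm contrast was used, the mean assumed for each arm, alpha and sidedness, and correct the calculation accordingly. Keep a record of how 32 was chosen rather than overwriting it.
- Justify the SD on the scale of the analysis instead of using 0.5.
- Add the detectable difference from the blinded data: about 6.2 percentage points at 32 analysed per arm (4.7 to 9.3 over the SD's 95% interval), or about 6.4 points at 30 per arm. Label it as erythrocyte-only and untransformed, and restate it on the transformed scale once the transformation is fixed.
- Reword the Results statement on adequate power to refer to the corrected figures, and do not extend it to plasma without a plasma SD.

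The cost is one rewritten paragraph and a short recalculation from pooled data already in hand. Masking is preserved and enrolment need not change.

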## Results

Recruitment into the study has proceeded as planned (Table 4). The majority of participants have been referred by their health care provider, particularly those who see a neurologist. Other participants are self-referred, having learned about the study through UNC advertisements, brochures, flyers, friends and family.

**Table 4 T4:** Recruitment for the exploratory analgesic dietary intervention for chronic daily headache, May 2010

	N	Percent
Inquiries about study	183	
Potentials to be screened	59	32.2
Screened	124	67.8
Eligible, but declined to participate	5	4.0
Ineligible at telephone screen	35	28.2
Headache characteristics	15	42.9
Medical/psychiatric problems	4	11.4
Logistic problems (time/distance)	11	31.4
Dietary Issues	2	5.7
Other/unknown	3	8.6
Scheduled for baseline consent	84	68.3
Ineligible at baseline consent	5	6.0
Eligible at baseline consent	79	94.0
Withdrew/ineligible before randomization	10	11.9
Withdrew after randomization	5	6.0
Awaiting baseline visit	18	14.5
Enrolled	46	37.9
Referral pattern		
Health professionals*	126	72.0
Electronic advertisements	32	18.3
Print advertisements	12	6.9
Family/Friends	2	1.1
Prior Study	3	1.7
Unknown	8	

* Health professionals that referred patients to the study included neurologists, family physicians, and nurses.

At this time, 124 individuals have been screened for eligibility of which 63 were enrolled into the study. Five enrolled individuals were ineligible to begin the dietary intervention due to low headache frequency (3), an intervening illness (1), or failure to keep up with the diaries. In addition to those who did not qualify, 10 individuals withdrew after giving consent, 5 during the baseline phase and 5 during the diet phase. Of the 5 individuals who withdrew during the baseline phase, 4 cited scheduling difficulties and 1 moved out of town. Of the 5 individuals who withdrew after randomization, 3 cited difficulty adjusting to the diet, 1 became pregnant, and another withdrew due to a traumatic injury that was unrelated to the study diet.

Adherence with the daily diary has been excellent, with 83.3% of participants completing at least 80% of daily entries. Most have tolerated the diets well; they have demonstrated diet adherence via changes in erythrocyte fatty acids. Preliminary analysis of composite erythrocyte fatty acid data of the first 20 participants, with blinding preserved (i.e., both diet groups are analyzed together and investigators remain masked to diet group), reveals significant reductions in %n-6 in HUFA and n-6 AA and LA, and significant increases in n-3 EPA, DHA and the omega-3 index compared with baseline erythrocyte fatty acids over the 12-week intervention (Table 5).

**Table 5 T5:** Means of erythrocyte fatty acids over the 12-week intervention, Chronic Daily Headache study, May 2010

	Baseline (n = 20)		Week 4 (n = 20)		Week 8 (n = 20)		Week 12 (n = 18)	
	
Variable	Mean	95% CI	Mean	95% CI	Mean	95% CI	Mean	95% CI
Omega-3 index	4.4	3.9, 5.0	6.2	5.4, 7.1	7.0	5.9, 8.1	7.8	6.5, 9.0
% n-6 in HUFA*	76.3	74.5, 78.0	70.4	67.5, 73.2	67.4	63.7, 71.0	64.7	60.3, 69.0
DHA	4.0	3.5, 4.5	5.2	4.5, 5.8	5.7	4.9, 6.5	6.3	5.4, 7.3
EPA	0.46	0.39, 0.54	1.1	0.8, 1.3	1.3	0.95, 1.6	1.4	1.0, 1.8
AA	14.8	14.5, 15.2	14.4	13.7, 15.1	13.8	13.2, 14.5	13.7	12.9, 14.5
LA	11.5	10.8, 12.1	9.5	8.8, 10.2	9.3	8.6, 10.0	9.5	8.8, 10.3

* %n-6 in HUFA is the percentage of omega-6 fatty acid in total HUFA as calculated by: 100 × (20:3n-6 + 20:4n-6 + 22:4n-6 + 22:5n-6)/(20:5n-3 + 22:5n-3 + 22:6n-3 + 20:3n-6 + 20:4n-6 + 22:4n-6 + 22:5n-6 + 20:3n-9).

Abbreviations: HUFA, highly-unsaturated fatty acid; DHA, Docosahexaenoic acid; EPA, eicosapentaenoic acid; AA, arachidonic acid; LA, linoleic acid.

Based on our current rates of recruitment, we expect to have a sufficient number of participants to complete the study 2 1/2 years after the first patient was enrolled. Based on these numbers, we should have adequate power to test our hypothesis of differential %n-6 HUFA in both plasma and erythrocyte lipid pools. Examination of the clinical data of the study (HIT-6, daily diaries) should allow us to predict effect sizes for a larger clinical trial.

## Discussion

This protocol paper provides a detailed overview of design and implementation of a randomized, outpatient, clinical trial comparing two novel analgesic dietary interventions as a strategy for management of CDH. Results so far indicate excellent adherence with both diets, enabled by provision of food for more than 2 meals per day, expert dietary counseling, and extensive web-based educational tools to support the interventions. Participants in the study have demonstrated a willingness to keep study appointments, adhere to the diets, and complete daily headache diaries. In addition, quality control procedures have ensured that laboratory specimens are meeting the highest standards for processing.

Preliminary blinded analysis of erythrocyte fatty acid data indicates significant reductions in n-6 AA and %n-6 in HUFA, and significant increases in n-3 EPA, DHA and the omega-3 index (Table 5). These changes are statistically significant despite the composite analysis of both dietary groups, albeit with greater variability than expected for one diet alone. Importantly, it is not possible to determine if %n-6 in HUFA and n-6 AA were reduced in both, or only one, diet group from this preliminary analysis. It is also worth noting the significant reduction of n-6 LA in these first 20 participants. To our knowledge, this is the first demonstration of reduced LA in human tissues with dietary LA intake below 2 en%. Recently, metabolic derivatives of LA, including 9- and 13-hydroxyoctadecadienoic acid (9- and 13-HODE), were identified as an endogenous family of potent TRPV1 (endovanilloid) receptor agonists [49,50]. TRPV1 receptors are critically involved in the initiation and perpetuation of chronic pain, and TRPV1 antagonists have potent analgesic effects [51]. Therefore, the long-term consumption of diets that contain less than 2 en% as LA could promote analgesia by reducing the LA content in human tissues and subsequently down-regulating the synthesis of LA-derived TRPV1 agonists. The long-term consumption of the low n-6, and low n-6 plus high n-3 diets in our current trial could have important implications for central pain sensitization and human physical pain via altering the abundance and metabolism of LA, AA, EPA, and/or DHA. Full analyses of metabolic and clinical outcomes at study completion will provide novel data to help answer the following open questions:

1) Does the reduction of dietary n-6 LA and AA over a 12-week period decrease the abundance of LA and AA, and increase n-3 EPA and DHA, in human erythrocytes and plasma?

2) Does the reduction of dietary n-6 LA and AA decrease circulating levels of bioactive mediators derived from LA (e.g. endovanilloids) and AA (e.g. eicosanoids, endocannabinoids)?

3) Does the addition of n-3 ALA, EPA and DHA to low n-6 diets produce additional metabolic alterations?

4) Do low n-6, average n-3 diets and/or low n-6, high n-3 diets attenuate human physical pain? If so, are pain reductions correlated with alterations in tissue contents of specific fatty acids and/or their metabolic derivatives?

### Limitations

The primary methodological limitation for interpreting the primary outcome (%n-6 in HUFA) and other metabolic outcomes of this trial is the limited duration of 12 weeks. Industrialized populations consuming large quantities of LA-rich seed oils maintain large quantities of n-6 LA in adipose tissue. In the US, adipose tissue LA increased from about 6% of total fatty acids in 1960 [52,53] to about 18% in 1986 [54], which coincided with an increase in dietary LA from about 2 en% in 1909 to 7 en% in 1999 [55]. Because n-6 and n-3 fatty acids have a half-life of about 1 to 2 years in adipose tissue [56-58], the 12-week dietary period employed in this trial may not be of sufficient duration for plasma and erythrocyte PUFAs to reach dynamic equilibrium. Our preliminary blinded analysis of erythrocyte fatty acid data is consistent with the expectation that maximal reductions in plasma and tissue LA and/or AA may not occur over 12 weeks; AA and %n-6 in HUFA continued to decline, and EPA, DHA, and the omega-3 index continued to increase between 8 and 12 weeks (Table 5).

The primary methodological limitation for interpreting the clinical outcomes of this trial is the lack of a control group consuming average US amounts of individual n-6 and n-3 fatty acids. This will limit the ability to determine if changes in clinical outcomes (headache frequency, intensity, and quality-of-life) are due to the diets themselves, to the expectation of benefits associated with participation in a clinical trial, or to the placebo effect of the interventions. This study was not designed to test the clinical efficacy of the dietary interventions. However, the study does demonstrate that, with support, free-living subjects can successfully modify their diets enough to result in significant changes in erythrocyte fatty acids, setting the stage for a larger, fully powered randomized controlled trial of clinical efficacy in CDH or another chronic pain population.
